### Sample Size

The Minimal Clinically Meaningful Difference (MCID) on the COPM is indicated by a change in occupational performance scores of two points on a 10-point scale (Law et al., 2014). A minimum sample size of 46 dyads is required to detect the MCID with 90% power at a two-sided alpha of 0.05, assuming a population standard deviation in COPM scores of two points (Graham et al., 2013). For an ANCOVA analysis of a cluster RCT, this sample size must be multiplied by a design effect to account for the correlation structure of the data (Rutterford et al., 2015). The final sample size has thus been inflated to 84 dyads (spread evenly between 14 or more therapists) to account for clustering (design effect = 1.2), treatment contamination in the control group (20%), and participants lost-to-follow-up (15%). We seek to recruit a minimum of 42 dyads where the caregiver is of Māori ethnicity, to allow for an adequately powered subgroup analysis with 80% power to detect a difference in treatment effect on the COPM.

For post-intervention interviews, 10 Māori who have received a minimum of one high-fidelity OPC session will be successively invited to participate. This sample size is based on prior research (Walker et al., 2017) and will be adjusted according to information power (Braun & Clarke, 2022; Malterud et al., 2016).

In relation to blinding: First, a research fellow (RF), blinded to group allocation, will collect all outcome measures in both intervention and control groups. The RF will have no contact with therapists or access to study data about therapists. Second, dyads will be blind to group allocation. Therapists will not be blinded to group allocation but will be requested not to refer to their group allocation or OPC by name to caregivers and children. Third, the biostatistician will not be blinded however the statistical analysis plan and statistical analysis code will be prepared a priori to the collection of the 16-week outcome data to ensure that analysis processes are not influenced by the data collected.

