### Usual Care Group

The comparison group for this study will receive “Usual Care,” which is known to be highly variable in content and dose across Aotearoa/New Zealand (Widdowson et al., 2015), and internationally (Anaby et al., 2017). Although Usual Care as a control group is problematic (Levack et al., 2019), it remains the best choice in this translational study in which OPC effectiveness is being examined with minimal interruption to other aspects of service delivery.

Prior evaluations of usual care in community paediatric rehabilitation in NZ (Graham et al., 2020; Widdowson et al., 2015) indicate: Goal setting is documented about half of the time; goals seldom address changes in participation in life situations, but rather children's impairments and activities; methods vary from hands on (child) to hands off (talking-based) methods and from child-directed to caregiver-directed; discussion with caregivers during intervention ranges from collaborative to directive and advice-based; provision of advice appears to be a dominant model of practice. Each of these features are deviations from OPC processes. Several strategies are in place to enable the description of what occurs within Usual Care and monitor contamination with the OPC group, including analysis of casenotes (OPC-CA), audio recording and coding of treatment sessions (using the OPC-FM), and collection of dose, location and delivery format of sessions. In addition, the sample size estimate has been set conservatively given the expected variation within the Usual Care group. Data will be collected from each Usual Care therapy session until 16 weeks from the initial session.

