## Statistical Methods

Participant data will be analyzed as-randomized (intention-to-treat, ITT). Two-sided *P* values will be reported and an alpha of 0.05 used for the construction of confidence intervals and for determining statistical significance. The analysis will be performed using R specialist statistical software (R Core Team, 2021). A detailed statistical analysis plan (SAP) will be prepared by the study biostatistician and agreed upon by the PI prior to any analysis of the data.

Differences between groups in outcome measures (COPM scores, DASS-21, and PEDI-CAT scores at 16 weeks) will be estimated with 95% confidence intervals using a “constrained baseline analysis” where a linear mixed-effects model is fitted to the individual level data with time and treatment included as fixed effects. Correlations within the data will be accounted for by incorporating the following random effects; cluster, an individual within cluster, and time within cluster, and a Kenward–Roger correction will be applied due to the small number of clusters (Hooper et al., 2018). Psychometric analysis of therapist self-completed and researcher-completed OPC-FM scores will be conducted to assess the validity and reliability of this instrument. Researcher completed OPC-FM scores, Session Characteristics, and SRSs will be summarised first by a therapist, and then by the treatment group. Linear regression analysis adjusting for clustering will be used to estimate mean treatment group differences with 95% confidence intervals.

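### The 90% power claim for 84 dyads does not hold if the stated 20% control-arm contamination dilutes the effect in full; power is then about 86%, or about 81% allowing for 14 clusters

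*Protocol article*

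**What the plan says.** The Sample Size section takes as its target "a change in occupational performance scores of two points on a 10-point scale", "assuming a population standard deviation in COPM scores of two points". From these it states: "A minimum sample size of 46 dyads is required to detect the MCID with 90% power at a two-sided alpha of 0.05". It explains that an ANCOVA analysis of a cluster trial needs a design effect, and continues: "The final sample size has thus been inflated to 84 dyads (spread evenly between 14 or more therapists"), the three allowances being "to account for clustering (design effect = 1.2), treatment contamination in the control group (20%), and participants lost-to-follow-up (15"%). It does not show how they were combined, gives no diluted target difference, and states no baseline correlation.

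Three other places bear on the point:

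- Statistical Methods analyses dyads by randomized group (intention-to-treat) with a constrained baseline mixed model, and says that "a Kenward–Roger correction will be applied due to the small number of clusters".
- Limitations accepts that therapists in one agency may be in different arms, and names contamination as a resulting risk.
- Usual Care Group says that "the sample size estimate has been set conservatively given the expected variation within the Usual Care group".

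**The concern.** Loss to follow-up and contamination act on power in different ways. A dyad lost to follow-up takes information away, so dividing by one minus the loss rate is the usual allowance. A contaminated control dyad is still observed and still analysed as a control, but its outcome moves toward the OPC arm. The expected difference shrinks, and the required sample grows with the inverse square of that difference. For a 20% dilution the factor is 1/0.80² = 1.56, not 1/0.80 = 1.25.

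If the smaller factor was used, the trial has less power for a true 2-point effect than its stated 90%. A null primary result could then be read as stronger evidence against a 2-point effect than the design can give.

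**Working it through.** **Inputs.** From Sample Size: difference 2, SD 2, two-sided alpha 0.05, 46 dyads before inflation, design effect 1.2, contamination 20%, loss 15%, final 84 dyads over 14 therapists (6 each). From Trial Design: 1:1 allocation. From Statistical Methods: as-randomized analysis with a Kenward–Roger correction. Two inputs are assumptions: the share of the OPC effect that contaminated controls gain, and 14 − 2 = 12 degrees of freedom (df) as an approximation to the Kenward–Roger analysis.

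**Step 1: reproduce 46.** A two-sample t-test with difference 2 and SD 2 has 91.2% power at 46 dyads and 89.97% at 44. So 46 is the smallest even total reaching 90%.

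**Step 2: reproduce 84.**

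| Handling of the 20% | Formula | Result |
|---|---|---|
| Lost sample, multiplied | 46 x 1.2 / 0.80 / 0.85 | 81.2, rounded up to 6 x 14 = 84 |
| Lost sample, added to dropout | 46 x 1.2 / 0.65 | 84.9 |
| Dilution, contaminated dyads gain half the effect | 46 x 1.2 / 0.90² / 0.85 | 80.2, rounded up to 6 x 14 = 84 |
| Dilution, contaminated dyads gain the full effect | 46 x 1.2 / 0.80² / 0.85 | 101.5 |

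The lost-sample routes use the 20% as it stands. The half-effect route also reaches 84 but needs an assumption that the article does not state. Full dilution does not reach 84.

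**Step 3: power of 84 dyads.** Effective N = 84 x 0.85 / 1.2 = 59.5. With noncentrality = (difference / 2) x √(59.5 / 4), the noncentral t distribution gives:

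| Effect gained by the contaminated 20% | Expected difference | Noncentrality | Power, N − 2 df | Power, 12 df |
|---|---|---|---|---|
| None | 2.0 | 3.86 | 96.6% | 94.2% |
| Half | 2 x 0.90 = 1.8 | 3.47 | 92.7% | 88.9% |
| Full | 2 x 0.80 = 1.6 | 3.09 | 85.8% | 80.8% |

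The N − 2 column is like for like with the t-test that produced 46. The 12-df column adds a separate small-cluster penalty that is not due to contamination.

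**Step 4: what 90% would need under full dilution.** Recomputed at 1.6 points, the t-test needs 68 dyads before inflation, and 68 x 1.2 / 0.85 = 96. Scaling the stated 46 gives 101.5, so 102. With 12 df the figure is about 112.

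**Step 5: sensitivity to baseline adjustment.** If the 1.2 covers clustering only, a baseline correlation r reduces the SD to 2 x √(1 − r²). At 1.6 points, r = 0.35 gives about 90% (N − 2 df), and r = 0.5 gives 93.9% (90.4% with 12 df).

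**The case against.** A reader might infer that the authors certainly handled contamination wrongly and that the true power is 81–86%. The documents do not support that, for four reasons.

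- **The method is inferred.** The article prints no arithmetic, a half-effect dilution also rounds to 84, and the derivation may be in the supplementary full protocol, which is not shown. This stands.
- **Full transfer of the effect is an assumption.** Usual Care therapists do not receive the OPC training, so partial transfer is plausible, and at half effect the 90% holds on the t-test basis. This stands as a condition on the result. But the article gives 20% with no partial-effect qualifier, so full dilution is the direct reading.
- **The 1.2 is ambiguous.** It is labelled as the allowance for clustering, yet introduced as the design effect for an ANCOVA. If the baseline gain is not in it, a correlation of about 0.35 (N − 2 df) to 0.5 (12 df) restores 90%. No correlation is stated, so the gain cannot be credited, nor can it be ruled out.
- **The 81% is not due to contamination alone.** It includes the 12-df penalty, which is approximate and assumes exactly 14 therapists where the plan allows more.

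It can also be said that recruitment may run to 126 dyads, which under full dilution would give about 96% (93% with 12 df) at a design effect of 1.2. That growth depends on Māori recruitment and is not the basis of the 90% claim.

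**Conclusion.** The point holds in conditional form. If the stated 20% means that one control dyad in five gains the full OPC effect, and no baseline gain is credited beyond the 1.2, then 84 dyads have about 86% power for a true 2-point effect, not 90%. Allowing for 14 therapists lowers this to about 81%. With half the effect transferred, the figures are about 93% and 89%. Without dilution, 84 dyads would exceed 90% on either basis, so whether the claim holds turns on how contamination is treated, and the article does not say.

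The shortfall is moderate: even the lower full-dilution figure is above 80%. A secondary matter is the statement that the sample size is conservative given variation in Usual Care. The calculation uses one SD of 2, and none of its three listed allowances is for extra control-arm variance. The contamination allowance may be what was meant, but the text does not say so.

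**What to change.** Keep 84 dyads and revise the Sample Size text as follows:

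1. Treat contamination as a reduction in the expected difference, and state the share of the OPC effect that contaminated controls are assumed to receive.
2. State whether the 1.2 already includes the ANCOVA gain. If it does not, give the baseline correlation assumed.
3. Show the arithmetic from 46 to 84 and restate power on those assumptions. Under full 20% contamination with no further baseline gain, this is about 86% for a true 2-point effect, or about 81% with small-cluster degrees of freedom.
4. In Usual Care Group, justify the claim that the estimate is conservative, or remove it.

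The cost is wording only. No extra dyads are needed, but under full dilution the stated power becomes less favourable.

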## Study Groups

Pre-randomization, a retrospective case note audit will be conducted using the OPC Case-note Audit tool (OPC-CA) (Graham & Ziviani, 2021a) to indicate the extent to which “usual care” for all enrolled therapists aligns with OPC.

### Intervention Group

Therapists randomized to the OPC group will undertake the recommended minimum of 24 hours (Graham & Ziviani, 2021a) of OPC training over four weeks. Training involves the completion of eight two-hour teleconference sessions and an eight-hour self-directed study package. Therapists will be provided with a published OPC manual (Graham et al., 2021), and undertake practice with feedback from the trainer. No modifications to OPC are planned for this study.

#### Occupational Performance Coaching

Therapists trained in OPC are taught to commence by asking questions which guide caregivers to identify their preferred future as goal statements. Goals describe participation in life situations (Imms et al., 2016) and occupational performance (Graham & Ziviani, 2021b). Thus goals in OPC specify observable actions in the context of life situations (i.e., home, school, or community), and reflect the personally meaningful change from caregivers’ perspectives. Therapists learn to move conversations in OPC through a process of Collaborative Performance Analysis from extensive *envisioning* of the preferred future-state goal, *exploring* bridges and barriers to goal progress, and *engaging* caregivers through attention to their psychological needs for autonomy, relatedness, and competence (see Figure 2).

**Figure 2. fig2-00084174231160976:**
[figure not shown]
Collaborative Performance Coaching is a unique analytical technique within Occupational Performance Coaching (OPC).

Key elements of OPC are listed in the OPC Fidelity Measure (OPC-FM) https://www.otago.ac.nz/opc/resources, designed according to the guidelines of the Treatment Fidelity Group (Bellg et al., 2004).

In implementing OPC, therapists do not use specialized equipment or materials or undertake assessments of impairments. No hands-on or directive (e.g., therapist arranging environment) methods are used with either the caregiver or child unless requested by the caregiver in the context of trialing ideas for collaborative analysis of their usefulness.

#### OPC Dosage

Therapists will engage with caregiver–child dyads in sessions of OPC over a period of up to 16 weeks, whereby a therapy “session” is defined as a therapeutic interaction (i.e., non-administrative) of at least 30 minutes duration. Therapists anticipate three or more sessions for each dyad, and will deliver OPC to the caregiver alone, or to the dyad, either in-person in the home, community, or clinic setting, or via telephone/video conference. OPC sessions typically take 45–60 minutes but can range from 20 to 90 minutes. Data will be collected until either therapy ends, or 16 weeks from the initial therapy session. Fidelity to OPC will be monitored using the OPC-FM and the OPC-CA (Graham & Ziviani, 2021a).

### Usual Care Group

The comparison group for this study will receive “Usual Care,” which is known to be highly variable in content and dose across Aotearoa/New Zealand (Widdowson et al., 2015), and internationally (Anaby et al., 2017). Although Usual Care as a control group is problematic (Levack et al., 2019), it remains the best choice in this translational study in which OPC effectiveness is being examined with minimal interruption to other aspects of service delivery.

Prior evaluations of usual care in community paediatric rehabilitation in NZ (Graham et al., 2020; Widdowson et al., 2015) indicate: Goal setting is documented about half of the time; goals seldom address changes in participation in life situations, but rather children's impairments and activities; methods vary from hands on (child) to hands off (talking-based) methods and from child-directed to caregiver-directed; discussion with caregivers during intervention ranges from collaborative to directive and advice-based; provision of advice appears to be a dominant model of practice. Each of these features are deviations from OPC processes. Several strategies are in place to enable the description of what occurs within Usual Care and monitor contamination with the OPC group, including analysis of casenotes (OPC-CA), audio recording and coding of treatment sessions (using the OPC-FM), and collection of dose, location and delivery format of sessions. In addition, the sample size estimate has been set conservatively given the expected variation within the Usual Care group. Data will be collected from each Usual Care therapy session until 16 weeks from the initial session.

## Measures and Procedures

### Outcome Measures

#### Primary Outcome Measure

The primary outcome is children's participation in personally valued life situations, measured 16 weeks after the first recorded therapy session using the COPM (Law et al., 2014). The mean between-group difference will be calculated by adjusting for values at recruitment (T1, see Figure 1). All caregivers, and children with cognitive and communication skills at or above age 8, will be invited to identify up to five life situations which are important to them, allowing formulation of future-oriented participatory goal statements. Consistent with COPM guidelines, caregivers and children will rate current “performance” and then ‘satisfaction with performance’ on 10-point Likert scales. The “performance” scale is the primary outcome.

The COPM has robust psychometric properties with paediatric ND populations, and is widely considered to be a gold standard measure of individualized performance in areas of personal value (Cusick et al., 2006, 2007; Law et al., 2014) and participation (Sakzewski et al., 2007).

### Secondary Outcome Measures

#### Pediatric Evaluation of Disability Inventory Computer Assisted Technology (PEDI-CAT)

Children's activity and participation will also be measured using an online version of the PEDI-CAT (Speedy version) (Haley et al., 2011). Theoretically, therefore we anticipate that improvement in child-focussed goals on the COPM that were addressed in therapy may be associated with improvement in related PEDI domains, particularly Daily Activities, Mobility, and Social/Cognitive domains (Thompson et al., 2018). The PEDI-Cat uses statistical algorithms to select a minimal set of questions based on the child's age, gender, use of a mobility device, and responses to previous questions. Caregivers will indicate their child's ability in the domains of Daily Activities, Mobility, and Social/Cognitive Skills, and Responsibility on 4-point scale. Scaled scores and normative scores (T-scores and age-percentiles) are generated for each domain.

#### KIDSCREEN10

The child reported quality of life will be measured using the KIDSCREEN10. A summary score reflects the overall perceived quality of life and wellbeing. It is validated for children aged 8–18 years. Psychometric analysis indicates adequate reliability and validity (Ravens-Sieberer et al., 2010).

#### Depression Anxiety Stress Scales (DASS-21)

Caregiver mental health will be measured using the short form of the DASS-21 (Crawford & Henry, 2003). Parental mental health is an important consideration in family centred intervention for children with neurodisabilities. Prior research on OPC indicates that parental psychological state may be both a mechanism (Graham et al., 2010) and an outcome of OPC (Chien et al., 2020; Graham et al., 2013) hence DASS21 will be collected pre and post-intervention. The DASS21 is a self-report questionnaire with 21 items using a 4-point response scale to measure negative emotional states over the prior week. The DASS-21 has been shown to demonstrate acceptable to excellent internal consistency and concurrent validity (Antony et al., 1998), is widely used with caregivers of clinical paediatric populations (Poole et al., 2018; Rayan & Ahmad, 2017) and is sensitive to change following OPC (Graham et al., 2013).

### Mechanisms of Change and Fidelity

#### Session Characteristics

At the end of each therapy session all therapists will record the session format (in person, phone, video-conference), length (minutes), and location (i.e., home, pre/school, community, clinic), and who was present and actively involved (i.e., child, sibling, partner, other adult family, and other professionals named by role—e.g., “social worker”). Non-attendance of scheduled sessions will also be recorded to inform the economic analysis.

#### Session Rating Scale (SRS)

At the end of each therapy session, all caregivers will rate their perceptions of the therapeutic alliance using the SRS (Duncan et al., 2003) in which a 4-item visual analog scale is used to assess client perspectives of respect and understanding of practitioner, the relevance of goals and topics, client–practitioner fit, and overall alliance. The scale has robust psychometric qualities (Campbell & Hemsley, 2009).

#### OPC-FM

The OPC-FM (Graham & Ziviani, 2021a) is a brief measure of fidelity that distinguishes OPC from expert-led and impairment-oriented approaches and indicates the quality of OPC application. Iterations of the OPC-FM were applied to over 50 recorded OPC sessions, with 10 therapists, by six raters. Formal psychometric testing of the OPC-FM is needed and planned as part of secondary analyzes within this study. The OPC-FM measures the occurrence of behaviour and the quality of this behaviour, with 14 items focusing on therapist behaviour and four items focusing on client responses. A score of 80% or higher is believed to represent high fidelity to OPC.

To monitor fidelity, OPC group therapists will self-administer the OPC-FM following the initial session, and one subsequent self-selected session with each dyad. Experienced OPC trainers will also score the OPC-FM based on audio-recordings of sessions. Therapists will be provided individualized feedback on OPC fidelity and offered additional 1:1 training until fidelity reaches adequate levels, but will not be removed from the primary analysis. Separately, raters, blind to group allocation, will complete the OPC-FM on a random sample of audio recordings from both groups to identify contamination between groups and enable unbiased reporting of treatment delivery.

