### Additional Analyzes

Baseline therapist and dyad characteristics will be summarised for the whole ITT population using means (standard deviations), medians (interquartile ranges), and frequencies (percentages) as appropriate. Summaries will be tabulated by the treatment group but no hypothesis testing will be undertaken. Goals documented by therapists and identified in the OPC-CA for both intervention and control groups will be compared against goal criteria for OPC and reported descriptively (i.e., counts, percent) (Graham & Ziviani, 2021a).

Adjusted analysis of primary and secondary outcome measures (COPM, PEDI-cat, and DASS-21) will be undertaken by adjusting for the following baseline variables as fixed effects in the model; therapist profession (OT, PT, and SLT), therapist years of experience, caregiver–child socio-economic status, caregiver ethnicity (Māori vs. non-Māori), caregiver education level, caregiver DASS-21, child age, and child ND.

A sensitivity analysis will be conducted on the primary outcome using the as-treated population. Caregiver–child dyads will have been deemed to have received the intervention (OPC) if more than half (two out of the three) OPC-FM assessments (researcher-completed or bias-adjusted therapist self-completed) for the caregiver–child dyad score 80% or above.

The heterogeneity of treatment effects will be assessed using the framework presented by Kent et al., 2010. An outcome prediction score will be calculated for each participant using a multivariable linear regression model including selected baseline variables (excluding the treatment group). A second linear regression model will be fitted including the outcome prediction scores, treatment group, and interaction between the two as independent variables, and observed outcome scores as the dependent variable. In addition, subgroup analysis of Māori caregiver–child dyads is planned a priori. Where interaction effects are found, treatment effects with 95% CI will be presented by each subgroup in tabular form, with continuous predictors dichotomized into approximately equal-sized groups.

Interview data with Māori caregivers will be analyzed by senior Māori researchers using reflexive thematic analysis (Braun & Clarke, 2022). This analysis will be underpinned by Kaupapa Māori Research principles (Smith, 2013) that privilege the perspectives of Māori participants and ensure the interpretation of data is culturally appropriate (Jones et al., 2010).

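### The later session used to monitor each dyad's OPC fidelity is chosen by the therapist being monitored, so those scores, and the uses made of them, can be selectively favourable (minor)

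*Protocol article*

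**What the plan says.** The OPC-FM section of the Protocol article describes two streams.

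- **Monitoring (OPC group).** "OPC group therapists will self-administer the OPC-FM following the initial session, and one subsequent self-selected session with each dyad". In addition, "Experienced OPC trainers will also score the OPC-FM based on audio-recordings of sessions"; the article does not say which sessions these are or who picks them. The consequence is stated next: "Therapists will be provided individualized feedback on OPC fidelity and offered additional 1:1 training until fidelity reaches adequate levels". Low-fidelity therapists stay in the primary analysis.
- **Reporting (both groups).** "Separately, raters, blind to group allocation, will complete the OPC-FM on a random sample of audio recordings from both groups". The stated purposes are to detect contamination and to report delivery without bias. Nothing links this stream to feedback or training.

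On the cut-off, the section says: "A score of 80% or higher is believed to represent high fidelity to OPC".

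Two analyses draw on the scores. Under Statistical Methods, "Psychometric analysis of therapist self-completed and researcher-completed OPC-FM scores will be conducted". Under Additional Analyzes, the as-treated sensitivity analysis of the primary outcome counts a dyad as having received OPC "if more than half (two out of the three) OPC-FM assessments (researcher-completed or bias-adjusted therapist self-completed") reach 80% or above.

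**The concern.** A therapist who picks a session after the event knows how it went, and knows that a low score leads to feedback and an offer of more training. A session picked that way is not a sample of usual delivery. The initial session is not chosen, but it covers only first contact, so among self-ratings all later work with a dyad is represented by the chosen session.

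Two uses of the scores are exposed.

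1. **Extra training.** This is the plan's means of correcting weak OPC while the trial runs. If scores look better than usual delivery, it may be offered too seldom to therapists just below an adequate level. The Sample Size section allows for contamination of the control group but states no allowance for weak delivery in the OPC group.
2. **As-treated classification.** Adjusting self-ratings for bias addresses how generously a therapist scores a given session. It does not by itself address which session was put forward. A trainer and a therapist could agree exactly on a chosen session and both scores would still be high relative to usual delivery.

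**Working it through.** The documents give no figure for this point: no OPC-FM mean, no SD, no statement of how therapists choose. What follows is an illustration on assumed values.

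**Inputs from the Protocol article.** Cut-off 80% (OPC-FM). Three or more sessions anticipated per dyad (OPC Dosage), so normally two or more later sessions to choose from. 84 dyads over 14 therapists (Sample Size), so 84/14 = 6 dyads per therapist. As-treated rule: two of three assessments at 80% or above (Additional Analyzes).

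**Assumed.** Scores normal and independent with SD 8 points and no variation between dyads; true mean μ = 75% (or 78%, or 70%); accurate scoring; the therapist submits the best of k later sessions.

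**Step 1: one chosen session.** The expected maximum of 2, 3 and 4 standard normal values is 0.56, 0.85 and 1.03, so the chosen score exceeds a typical one by 4.5, 6.8 and 8.2 points. The chance of reaching the cut-off is 1 − Φ((80 − μ)/8)^k.

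| μ | pre-fixed (k = 1) | best of 2 | best of 3 | best of 4 |
|---|---|---|---|---|
| 75 | 27% | 46% | 60% | 71% |
| 78 | 40% | 64% | 79% | 87% |

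For μ = 75: Φ(0.625) = 0.734, and 1 − 0.734² = 0.46.

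**Step 2: a decision about a therapist.** Training is offered to therapists, so the single-session rates do not describe that decision. Suppose it rested on the mean of six initial and six chosen sessions. With no selection the standard error is 8/√12 = 2.31. With best of 2 the mean is μ + 4.51/2 and the standard error is 2.12. The chance that the mean reaches 80% is then:

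| μ | no selection | best of 2 | best of 3 | best of 4 |
|---|---|---|---|---|
| 70 | under 0.1% | under 0.1% | under 0.1% | 0.2% |
| 75 | 1.5% | 10% | 21% | 33% |
| 78 | 19% | 55% | 75% | 86% |

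If instead any initial session below 80% prompted feedback, a therapist would escape only when all six pass: 0.266⁶ = 0.0004 at μ = 75 and 0.401⁶ = 0.004 at μ = 78. Under that rule the choice of later session hardly matters. The article does not say which rule applies.

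**Step 3: the as-treated rule.** Let p be the chance for an unselected assessment and c the chance for the chosen one, with one of the three assessments chosen. Then P(at least two of three) = p² + 2p(1 − p)c. At μ = 75, p = 0.266:

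- no selection, c = 0.266: 0.071 + 0.390 × 0.266 = 0.17
- best of 2, c = 0.461: 0.071 + 0.390 × 0.461 = 0.25
- best of 3, c = 0.605: 0.071 + 0.390 × 0.605 = 0.31

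In every step, neutral choice gives the k = 1 result and no bias.

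**The case against.** The case on the other side is substantial, and most of it stands as a limit on the point.

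- **Monitoring does not depend on the chosen session alone.** The initial session with every dyad is fixed, about six per therapist. Trainers also score recordings, and the text does not restrict them to chosen sessions. The as-treated rule counts three assessments, so at least one beyond the two self-ratings is expected. This stands.
- **Silence on which recordings trainers score is not a finding.** The article condenses a full protocol that is not shown here. This stands, and the point does not rely on that silence. It relies on what is stated: the therapist selects the later self-rated session.
- **Clearly low fidelity would tend to be seen.** Step 2 agrees: at a true mean of 70% selection almost never hides the problem under either rule. The exposed group is borderline therapists.
- **Favourable choice is assumed.** It is plausible but not shown.

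A reader might infer that reported fidelity will be inflated. The documents do not support that, because delivery is to be reported from a separate random sample rated blind to group. A reader might also infer that the 16-week COPM result is biased in favour of OPC. That is not supported either: dyads are analysed as randomized, and missed training would tend to weaken the contrast. No figure in the documents links missed training to a COPM difference. Finally, one might infer that the comparison of self-completed with researcher-completed scores rests on a narrowed range of sessions. The article does not say which sessions form those pairs, so this is only a possibility.

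What remains is that the person monitored chooses part of the monitoring data, and the random sample that would avoid this is kept separate from the training loop.

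**Conclusion.** The point holds in limited form, and its severity is minor. The later session self-rated for each dyad is selected by the therapist being monitored. If the choice is favourable, three things can follow: later-session scores overstate usual delivery, some borderline therapists miss the offered training, and self-completed scores in the as-treated rule carry a selection bias that a self-rating adjustment need not remove.

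The size is unknown. The illustration puts the shift in a chosen score at 4.5 to 8.2 points, and the share classed as treated at 25% to 31% instead of 17% at a true mean of 75%. All of this rests on an assumed mean and SD, accurate and independent scoring, and deliberate choice of the best session. The primary analysis remains a valid comparison of the groups as randomized; the worst plausible effect on it is some dilution.

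**What to change.** In the OPC-FM section, replace the therapist's choice of later session with one of the following:

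- a later session fixed in advance by attended-session number, or the last session if therapy ends sooner; or
- a session drawn by the study team from the later recordings that exist for the dyad.

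Use that same session for the self-rating, the trainer rating and the as-treated classification. Therapists may still self-score other sessions for their own learning, outside the monitoring data.

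The fixed number is the simpler option. A draw is only as good as the set of recordings, and the article does not say that every later session is recorded. If the number is set early, feedback can still help the same dyad.

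The cost is about one sentence in the fidelity procedure and no additional self-ratings. The downside is that therapists lose the choice of session for formal feedback.
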